## Discussion

The MATCH study was the first national prospective registry for AVMs in mainland China. This study is dedicated to exploring the current status of AVM treatment in mainland China (covering most provinces, municipalities, and autonomous regions) and identifying the natural history of AVMs in the Asian population. In addition, this study wants to investigate traditional and emerging hemorrhagic predictors, and explore the superiority of the multidisciplinary assessment in improving the long-term outcomes. On this basis, we will explore the optimal individualized treatment strategies.

Ruptured AVMs should be actively intervened because of the high re-rupture risk [8, 19]. However, the teatment options for unruptured AVMs are currently controversial [20]. ARUBA was the first trial to compare the effects of medical therapy and intervention. During the 33-month follow-up, the medical therapy proved superior in preventing stroke and death [11]. However, the results were strongly criticized regarding several aspects of study design, progression, analysis, and conclusions [21]. Many neurosurgical centers even reported contrary results [22, 23]. However, in 2020, the ARUBA research team reached the final results of ARUBA after long-term follow-up (50.4 months) of 226 patients: medical management alone remained superior to intervention for the prevention of death or symptomatic stroke in unruptured AVMs [12]. After that, a study from the National Inpatient Sample in the USA suggested that the ARUBA trial has influenced the treatment pattern of unruptured AVM, with the overall treatment rate of unruptured AVM decreasing [24]. However, it is worth considering whether medical therapy can benefit the clinically assessed AVMs at high rupture risk (such as combined with exclusive deep venous drainage, and flow-related aneurysm). Therefore, exploring an individualized and optimal treatment protocol based on rupture risk assessment and long-term neurological prognosis prediction is necessary.

Three AVM-related registration trials are cited in PubMed and recruiting currently. The first study, the Treatment of Brain AVMs (TOBAS), started recruiting in 2015 [25]. The general objective is to offer a care trial context for the management of ruptured and unruptured AVMs. In 2017, the TOBAS research team reported encouraging single-center recruitment rates and 61 patients were enrolled in the registry study [26]. The second study, the Multicenter AVM Research Study (MARS) study, an international observational cohort study, concentrated on the long-term outcomes and hemorrhagic predictors in unruptured AVMs [27]. In 2014, the MARS investigators reported that hemorrhagic presentation and increasing age were independent predictors of AVM rupture. It should be noted that MARS will perform causal analysis between the randomized data (ARUBA) and observational data (MARS). The third study, the New ASSessment of cerebral Arteriovenous Malformation yet Unruptured (NASSAU) study, a retrospective study comprising multicenter data from 1351 ARUBA-eligible patients who underwent Gamma Knife Surgery (GKS) [28]. They suggested that the period to break even for morbidity and mortality of AVMs treated with GKS compared to untreated patients in ARUBA was found to be 5 years. The NASSAU is a well-conceived study and reveals the severe limitations of ARUBA.

Exception for the TOBAS study, most of the aforementioned registry studies only focus on unruptured AVMs, and the current disclosed data in the TOBAS study are not encouraging in terms of the recruitment of participating centers and patients. Besides, the optimal intervention strategy for ruptured AVMs remains elusive, especially in patients with similar interventional indications or complex angioarchitecture. The MATCH study can better address this gap as the nationwide prospective registry that can provide adequate samples for prognostic analysis of each treatment strategy and can support the establishment of the prognostic prediction model. Of course, the MATCH study will also explore optimal treatment strategies for unruptured AVMs and develop predictive models that can accurately predict long-term outcomes, and compare the predictive performance with previous models [29].

Another strength of the MATCH study was that novel hemodynamic parameter are introduced and will be used to create rupture prediction models with better predictive performance than previous models [4]. The characteristic angioarchitecture is caused by specific hemodynamics. Color-coded DSA is a breakthrough research direction in recent years for AVM hemodynamic studies [16, 17, 30], and the MATCH study will explore it in depth. The MATCH study will use the NCC study to explore and validate hemorrhagic predictors and build rupture prediction models based on this, which is expected to provide precise prediction of future cerebrovascular events in AVMs. Besides, the MATCH study will explore the superiority of multidisciplinary comprehensive assessment, promote the formulation of individualized treatment protocols conducted by multidisciplinary teams, and effectively promote precision medicine.

There are several limitations of MATCH. First, despite being represented as a whole, potential selection bias of patients was unavoidable since the selected neurosurgical center in this study mostly represented the hospitals with more medical resources and expertise than the low-level hospitals. Second, the MATCH study did not involve the uniform collection and analysis of biological samples from multiple centers due to research funding constraints. Third, the Multidisciplinary Professional Committee of MATCH developed the multidisciplinary standardized treatment protocol to reduce workload. However, the protocol contains overlapping indications between different treatment strategies, which would lead to the deviation of grouping. The multidisciplinary team will decide whether to classify them as experimental or control groups at the regular meetings. Finally, the experimental group has significant less samples than the control group, but with the integration and promotion of the multidisciplinary model, the difference in sample size will be eliminated.

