### Clinical management

Conservation, microsurgery, embolization, SRS, and multimodal strategies are all included in this study. Patients will be divided into experimental and control groups according to whether the treatment protocols were formulated by a multidisciplinary team. In order to reduce workload, the MATCH Research Organizing Committee developed a standardized treatment protocol of multidisciplinary assessment as follows:

Ruptured AVMs: (1) microsurgery: microsurgery is recommended for AVMs not located in deep critical eloquent areas (brainstem, thalamus, basal ganglia, etc.) or more than 5 mm away from functional fiber bundles, regardless of the SM grade; (2) embolization: embolization should be performed 2–6 weeks after rupture; target embolization for hemorrhagic predictors could be considered as a monotherapy; palliative embolization can be used as an adjunctive strategy to reduce blood flow or nidus volume before microsurgery or stereotactic SRS; (3) SRS: SRS is indicated for patients with a nidus volume < 10 ml and not in the acute phase of hematoma (< 3 months); volume-stage or dose-stage can be used for giant AVMs. (4) Multimodality: the multimodality strategy such as single-stage combined embolization + resection (hybrid surgery) or staged embolization + resection or adjunctive embolization + resection/SRS or adjuvant SRS + resection are indicated for complex AVMs, such as giant AVMs involving deep eloquent areas, or AVMs with complex blood supply. (5) Conservation: conservation can be used for AVMs that are prone to severe disability due to intervention.

Unruptured AVMs: interventions are recommended if unruptured AVMs are assessed as being at high rupture risk or having refractory epilepsy or acceptable postoperative neurological deficits; otherwise, conservative treatment is recommended. The rupture risk stratification will be assessed qualitatively and quantitatively by the multidisciplinary team based on their own experience and the rupture prediction model to facilitate the division of the experimental and control groups. Regular multidisciplinary discussion meetings and fixed multidisciplinary groupings will ensure consistency of analytical results. Besides, the choice of intervention is the same as for ruptured AVMs.

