It should be noted that the AVM multidisciplinary team for the MATCH study was established in June 2018, so the previously collected prospective AVM cohort from August 2011 to June 2018 and the AVM cohort after June 2018 without comprehensive evaluation by the multidisciplinary team served as the control group.

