## Results

Patient recruitment is still ongoing, and we now summarize the data in stages as follows: Between August 2011 and April 2021, 3653 brain AVM patients were consented and registered to the MATCH study in 11 participating sites. After rigorous screening, a total of 412 patients were excluded. Finally, a total of 3241 AVMs fulfilled the initial inclusion criteria. Among them, 15.43% (500 AVMs) underwent multidisciplinary assessment and received standardized treatment as prescribed by MATCH. The detailed patient enrollment flow chart is shown in Fig. 2. The included patients had similar baseline demographic, clinical, and imaging characteristics as those excluded (Table 2).

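### From June 2018 on, the multidisciplinary team's own judgement can enter the experimental/control label, so the superiority comparison is open to bias that PSM and IPTW cannot remove

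*Protocol article*

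**What the plan says.** The basic rule is in Methods, Clinical management: "Patients will be divided into experimental and control groups according to whether the treatment protocols were formulated by a multidisciplinary team". The end of that section adds that the team was set up in June 2018. Patients collected from August 2011 until then are controls, and "the AVM cohort after June 2018 without comprehensive evaluation by the multidisciplinary team served as the control group". These two statements agree with each other: the exposure is evaluation and planning by the team.

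Three other statements do not fit that rule cleanly.

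- Clinical management, paragraph on unruptured AVMs: the team grades rupture risk "based on their own experience and the rupture prediction model to facilitate the division of the experimental and control groups".
- Discussion, limitations: "the protocol contains overlapping indications between different treatment strategies, which would lead to the deviation of grouping". The remedy offered is: "The multidisciplinary team will decide whether to classify them as experimental or control groups at the regular meetings".
- Results, first paragraph: the experimental patients are described as those who "underwent multidisciplinary assessment and received standardized treatment as prescribed by MATCH", which is assessment and treatment received together.

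Superiority of multidisciplinary assessment is one of the main objectives (Study objectives). The primary outcome is mRS at 3 years after treatment (Outcomes measurements). PSM and IPTW are the planned adjustment in the cohort studies (Statistical analysis).

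**The concern.** In a non-randomised comparison, the exposure label should follow from a recorded fact at a known time. Here part of it is a judgement by the team whose benefit is being tested. The judgement draws on rupture risk, which is a prognostic factor, and on how a case fits the treatment protocol. If patients with a better or worse expected course are sorted into one group, the groups will differ at 3 years even when team assessment does nothing.

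PSM and IPTW balance measured baseline covariates between groups whose membership is taken as given. They do not correct for unrecorded expert judgement used in setting the label, or for a label that depends on what treatment was given after the assessment. At stake is whether a difference in 3-year mRS can be read as an effect of multidisciplinary assessment.

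**Working it through.** **1. The document's own figures.** 3653 − 412 = 3241 included. 500 + 2741 = 3241. 500/3241 = 15.43%, as stated. Pearson chi-square tests without continuity correction reproduce the tabulated p-values that were checked in Tables 3 and 4: hemorrhage 0.927, conservation 0.659, microsurgery 0.237, supratentorial location 0.081, loss to follow-up 0.071. The article states no effect size or power for this comparison, so there is no planned figure to reproduce.

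**2. The statements side by side.**

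| Place | What decides the label |
|---|---|
| Clinical management, opening | Team formulated the plan |
| Clinical management, end | Enrolment date; evaluated by the team or not |
| Clinical management, unruptured AVMs | Team's risk stratification helps the division |
| Discussion, limitations | Team decides for overlap cases |
| Results (a description) | Assessed and given the standardized treatment |

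The first two rows are one rule. Under that rule, overlap between treatment indications could not disturb the grouping: a patient is evaluated by the team or is not, whichever treatment is chosen. The Discussion says overlap does disturb it. That makes sense only if the fit between patient, treatment and standardized protocol also enters the label. The Results description points the same way but is not itself an allocation rule.

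**3. What size of effect this could have.** Assumptions, none of them from the document: mRS is split into good and poor; the poor-outcome rate is p = 15% or 25% in everyone (no true effect); outcomes are complete; there is no adjustment. Treat the 500 as the pool of team-assessed patients. A share f of them is moved to control, and those moved have r times the average risk.

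- Experimental: pE = (p − f·r·p)/(1 − f), with n = 500(1 − f)
- Control: pC = (2741p + 500f·r·p)/(2741 + 500f)
- OR = [pE/(1 − pE)]/[pC/(1 − pC)]
- Chance of two-sided p < 0.05: normal approximation with the pooled variance

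Example with p = 0.15, f = 0.05, r = 1.5, so 25 patients move at risk 0.225:

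- pE = (0.15 − 0.01125)/0.95 = 0.1461
- pC = (411.15 + 5.625)/2766 = 0.1507
- OR = 0.96

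| p | f | r | Experimental | Control | OR | Chance of p < 0.05 |
|---|---|---|---|---|---|---|
| 15% | 5% | 1.5 | 14.6% | 15.1% | 0.96 | 5.8% |
| 25% | 5% | 1.5 | 24.3% | 25.1% | 0.96 | 6.5% |
| 15% | 10% | 2 | 13.3% | 15.3% | 0.85 | 18.7% |
| 25% | 10% | 2 | 22.2% | 25.4% | 0.84 | 31.1% |
| 15% | 20% | 2 | 11.3% | 15.5% | 0.69 | 61.2% |
| 25% | 20% | 2 | 18.8% | 25.9% | 0.66 | 86.9% |
| either | any | 1 | p | p | 1.00 | 5.0% |

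**4. Direction.** If those moved have a lower than average risk, the sign turns. With p = 0.15, f = 0.10, r = 0.5:

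- pE = (0.15 − 0.0075)/0.90 = 0.1583
- pC = (411.15 + 3.75)/2791 = 0.1487
- OR = 1.08, against the experimental group

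**The case against.** The strongest reply is that the discretion is narrow and disclosed. The patients the team classifies are most naturally those with overlapping indications, and everyone before June 2018 is a control by date. The definition of later controls at the end of Clinical management is already close to a clean rule. The risk-stratification phrase stands only in the paragraph on unruptured AVMs and gives no criterion. The Results sentence describes 500 patients and does not say that anyone assessed but treated differently was moved to control. All of this stands and limits the point to part of the post-2018 cohort. Every experimental patient comes from that period, however, and there are only 500 of them, so a modest number of moves matters.

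A second reply is that the groups look alike. Hemorrhagic onset is 61.1% against 61.4%, the admission mRS median and IQR are the same, all nine treatment rows in Table 3 have p of at least 0.123, and Spetzler-Martin grade has p = 0.348. This speaks against strong selection on those measured factors. It does not exclude selection on what experienced clinicians see and the form does not record.

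Disclosure as a limitation does not settle the matter, because the remedy disclosed is the discretionary decision itself.

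A reader might go further and infer that labels are set with knowledge of outcome, or that the comparison favours the experimental group. The document supports neither. It does not say when the label is fixed. Although 191 multidisciplinary patients had already completed 3 years, nothing says that any label was set or changed after follow-up. If 25 patients, all with poor outcomes, were moved at p = 15%, the result would be 10.5% against 15.8% (OR 0.63). That is a worst case resting on a mechanism the document does not describe.

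**Conclusion.** The point holds in limited form. The article states a usable exposure rule and then lets the team's prognostic judgement, and its decision on overlap cases, enter the label without criterion or time point. Dependence on prognosis follows from the text. Dependence on treatment received is supported by the Discussion and Results but not stated as a rule. Dependence on outcome is merely not excluded. The comparison is therefore open to bias; it has not been shown to be biased.

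Size and direction cannot be derived from the document. Under the assumed rates the effect runs from none (moves unrelated to prognosis), through an OR of about 0.96 (5% moved, relative risk 1.5), to 0.84 to 0.85 (10% moved, relative risk 2), and can reverse. Because this concerns a main objective and lies in what the document states, it should be settled before the superiority comparison is analysed.

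**What to change.** Reconcile the statements in Clinical management, Results and Discussion into one rule:

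- A patient is experimental if and only if a multidisciplinary team assessment was documented and dated before the first treatment started or, for conservative management, before that plan was adopted. All others are control. Tying the date to the start of treatment, not to the treatment decision, matters because the team's assessment is itself that decision.
- The label is fixed at that date. Remove the team's discretion over overlap cases, and the phrase on risk stratification, from the group definition.
- Analyse by this label whatever treatment was received. Report adherence to the standardized protocol as a secondary result.
- Check the existing 500/2741 split against the rule where dated records exist, and report how many labels cannot be verified.

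The cost is a change of wording, a date field in the EDC if there is none, and a one-off check of existing labels. How much work the check takes depends on records the article does not describe. The experimental group may then include some patients treated off the standardized protocol, which may slightly dilute the effect. Enrolment is planned to April 2032, so the rule can still govern much of the experimental cohort. Nothing in it changes how patients are treated.

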## Conclusion

The MATCH study is a large-sample nationwide prospective registry to investigate multimodality management strategy for AVMs. Data from this registry may also support individualized rupture risk assessment and optimal management strategies selection.

## Data Availability

All data relevant to the study are included in the article or uploaded as supplementary information.

## Abbreviations

ARUBA: A Randomized Trial of Unruptured Brain Arteriovenous Malformations AVMArteriovenous malformation
DTI: Diffusion tensor imaging
DSA: Digital Subtraction Angiography
EDC: Electronic Data Capture
FWHM: Full width at half maximum
GKS: Gamma Knife Surgery
IQR: Interquartile range
IPTW: Inverse probability of treatment weighted
mRS: Modified Rankin Scale
MARS: Multicenter AVM Research Study
MATCH: Multimodality treatment for brain ArTeriovenous malformation in mainland CHina
MRI: Magnetic resonance imaging
NCC: Nested case-controlled
PSM: Propensity score matching
NASSAU AVMs: New ASSessment of cerebral Arteriovenous Malformation yet Unruptured
ROCs: Receiver operating curves
SD: Standard deviation
SRS: Stereotactic radiosurgery
SWI: Susceptibility-weighted imaging
3D T1w MPRAGE: Three-dimensional T1-weighted Magnetization Prepared Rapid Acquisition Gradient Echo
3D-TOF MRA: Three-dimensional time-of-flight MR angiography
TTP: Time to peak
TRV: Trans-nidal relative velocity
TOBAS: Treatment of Brain AVMs
2D T2w: Two-dimensional T2-weighted
